## Abstract

**Background:**

Suicide is a major public health problem worldwide. In the UK suicide is the second most common cause of death in people aged 15-24 years. Self harm is one of the commonest reasons for medical admission in the UK. In the year following a suicide attempt the risk of a repeat attempt or death by suicide may be up to 100 times greater than in people who have never attempted suicide.

Research evidence shows increased risk of suicide and attempted suicide among British South Asian women. There are concerns about the current service provision and its appropriateness for this community due to the low numbers that get involved with the services. Both problem solving and interpersonal forms of psychotherapy are beneficial in the treatment of patients who self harm and could potentially be helpful in this ethnic group.

The paper describes the trial protocol of adapting and evaluating a culturally appropriate psychological treatment for the adult British South Asian women who self harm.

**Methods:**

We plan to test a culturally adapted Problem Solving Therapy (C- MAP) in British South Asian women who self harm. Eight sessions of problem solving each lasting approximately 50 minutes will be delivered over 3 months. The intervention will be assessed using a prospective rater blind randomized controlled design comparing with treatment as usual (TAU). Outcome assessments will be carried out at 3 and 6 months. A sub group of the participants will be invited for qualitative interviews.

**Discussion:**

This study will test the feasibility and acceptability of the C- MAP in British South Asian women. We will be informed on whether a culturally adapted brief psychological intervention compared with treatment as usual for self-harm results in decreased hopelessness and suicidal ideation. This will also enable us to collect necessary information on recruitment, effect size, the optimal delivery method and acceptability of the intervention in preparation for a definitive RCT using repetition of self harm and cost effectiveness as primary outcome measures.

**Trial Registration:**

Current Controlled Trials 08/H1013/6

## Background

Prevention of suicide is a priority for health services in England [1]. Among the ethnic minority groups in UK there are reports of high rates of suicide in South Asian women [2]. Studies done previously in the UK similarly suggest that rates of self harm in British South Asian women are higher compared to the white population [3,4]. Of the known risk factors for suicide, the most strongly predictive of a future suicide attempt or completed suicide, are hopelessness and a prior history of self harm [5]. In Manchester data collected in Emergency departments over a four-year period showed a higher rate of self harm in South Asians than white European females (relative risk 1.5 times in 16-24 years age group). Interpersonal conflicts within the family were the main precipitating factor, which were significantly more frequent in South Asians than in white females. In spite of no differences in clinical presentation and suicidal intent, there were significant differences in the management of the two groups. Referral back to primary care was the most common management plans for South Asians, while European whites were referred to psychiatric services for further management [6,7].

In our previous study in primary care (Husain et al, 1997) and in the population based study [8] concerning the mental health needs of people of Pakistani family origin, we reported that women of Pakistani origin living in the north west of England have high rates of emotional distress and depression. A total of 13.8% of the 475 Pakistani women reported suicidal ideation on Self Rating Questionnaire (SRQ). This was associated with increased psychological distress (mean SRQ score of 12.3 in participants with suicidal ideas as compared to 5.23 in those who did not report suicidal ideas) [9]

Studies in the UK have reported socio- cultural determinants as contributing factors for depression such as cultural conflict within families particularly around family values, conflict in areas such as personal choices in relationships, jobs, pressure from family to conform to arranged marriages [10]. A previous qualitative study has demonstrated that young South Asian women access care only in times of crisis as a last resort and not early on when problems initially start [11]. It is suggested that services fail to engage with ethnic minorities [12]. Following an episode of self harm due to lack of appropriate treatment offered or a negative impact of services British South Asian women may feel reluctant to present again to services after a further self harm episode. The higher rate of suicide in young women of South Asian origin may be related to untreated self harm [13]

Self harm in British South Asian women may be due to their culturally related psychosocial stressors, there is evidence in literature that problem solving therapies [14] and interpersonal psychotherapy [15] has helped those who self harm. These therefore may also help women of British South Asian origin. The interventions will have to be adapted to meet the specific needs of this group. As most episodes of self harm are following a family conflict there is a strong case for demonstrating the effectiveness of an intervention which is able to address such cultural specific issues.

Problem solving therapy has a sound theoretical basis. Consistent evidence has shown that people who attempt suicide have poor problem solving skills [16]. It is hypothesized that problem-solving deficits contribute to hopelessness and depression, which in turn increase the probability of suicidal ideation and intent [17]. Problem solving therapy has been found to be effective in reducing levels of depression and hopelessness in patients who have attempted suicide [18]. In addition problem-solving therapy is a brief, cost effective, pragmatic intervention that has the potential to be widely utilized in clinical practice. Thus a strong rationale exists for the exploratory trial of problem solving therapy in order to clearly determine the acceptability of this intervention following self harm in British South Asian population.

### Aims and objectives

In preparation for a future definitive randomized control trial using repetition of self harm and cost effectiveness as the outcome measures, in this pilot trial we aim to collect necessary information on the assessment instruments, effect size, the optimal delivery and acceptability of the intervention. We also want to gauge the optimum length of treatment and to evaluate the therapy in a preliminary way to see if we can determine a treatment effect.

A further aim is to determine whether C- MAPS compared with treatment as usual results in decreased hopelessness and suicidal ideation. We will explore the impact of the intervention on patient's resolution of interpersonal and family problems to fully understand the mechanism of action of C- MAPS.

## Methods

We will conduct a pilot randomized controlled trial of culturally adapted manual assisted Problem Solving Therapy (C- MAPS) in British South Asian females who self harm. Ethical approval was obtained from Tameside &Glossop Local Research Ethics Committee for the study (REC Reference number: 08/H1013/6). The intervention will be assessed using a prospective rater blind randomized controlled design, with an experimental and a control treatment as usual (TAU) group. Face to face baseline interviews followed by 3 months outcome assessments will be carried out. Further six months follow up assessments will be through post or telephone. A sub group of participants will be invited for in depth qualitative interviews exploring about barriers accessing mental healthcare and family dynamics.

### Inclusion Criteria

All 16-65 years old self ascribed British South Asian women presenting to emergency department or at the general practices after an episode of self-harm will be invited to participate in the trial. Participants should be resident in the trial site catchment area and be able to communicate in Urdu, Hindi, Punjabi or English.

Self harm will be defined as self inflicted injury, and/or ingestion of drugs in excess of the recommended therapeutic dose, with some intention of ending one's life [19]

### Exclusion Criteria

Temporary resident unlikely to be available for follow up, those fulfilling the ICD 10, Research diagnostic criteria for Organic brain disorders, Alcohol and drug dependence, Schizophrenia and Bipolar Affective Disorders, and patients who require psychiatric admission after an episode of self-harm will be excluded from the study.

### Trial Centers & Proposed sample size

East Lancashire and Greater Manchester have a large South Asian population [20]. From the case records we know that around 100 patients of South Asian origin present to the emergency departments/GP practices over a 12 months period. We propose to recruit enough patients so that we have at least 10 patients in the experimental group.

### Recruitment plan

The study will be conducted at the emergency departments of Royal Blackburn, North Manchester General and Manchester Royal Infirmary hospitals and GP practices that cover areas with large South Asian population. We will be using culturally appropriate strategies to promote the trial. Liaison with the community has already been initiated through awareness talks in partnership with the voluntary sector organizations. These voluntary organizations were also invited to comment on the design of the trial and content of the intervention. Information about the study in the form of posters and information sheets in the four study languages (Urdu, Hindi, Punjabi and English) will be made available. The therapists in the team are also proficient in these south Asian languages. The research team will also conduct regular liaison meeting with the emergency department, crisis team staff and GP practices to promote the study within the departments.

Consecutive patients meeting inclusion criteria will be informed about the study by the clinician who will take verbal or written consent for the research team to make the contact.

The study will be explained to each participant in detail by a researcher and written consent will be obtained. Family participation will be encouraged but only with participants' permission. For randomization the researcher will refer to an allocation sequence that will be provided by the offsite trial statistician and based on a computer generated list of random numbers. Even if there is more than fifty percent refusal we expect sufficient number of patients each assigned to C- MAPS or the treatment as usual group.

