### Outcome measures

#### Primary outcome measure

*Beck scale for suicidal ideation: *A 21-item self-report questionnaire used to detect and measure severity of suicide ideation [25]

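### As described, allocation concealment is not protected: the researcher who explains the trial before consent also consults the allocation sequence, and the rater-blind statement has no described procedure behind it

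*Protocol article*

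**What the plan says.** The protocol article describes the path into the trial in its Recruitment plan section:

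- Consecutive eligible patients are "informed about the study by the clinician who will take verbal or written consent for the research team to make the contact".
- The research team then takes over: "The study will be explained to each participant in detail by a researcher and written consent will be obtained".
- Allocation follows: "For randomization the researcher will refer to an allocation sequence that will be provided by the offsite trial statistician", and the sequence is "based on a computer generated list of random numbers".

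On blinding and assessment, the Methods section says: "The intervention will be assessed using a prospective rater blind randomized controlled design". The abstract makes the same claim. Methods adds: "Face to face baseline interviews followed by 3 months outcome assessments will be carried out", and "Further six months follow up assessments will be through post or telephone". The primary outcome, the Beck scale for suicidal ideation, is "A 21-item self-report questionnaire used to detect and measure severity of suicide ideation". The Sample Size section sets a total of 30 participants in two groups.

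**The concern.** Generating a sequence well and concealing it are separate safeguards. An offsite statistician and computer-generated random numbers secure the first. The second requires that whoever enrols a participant cannot learn the next assignment until she is irrevocably in the trial. The article describes a mechanism for this step, and in it the research team consults the sequence.

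If the recruiting researcher knows the next arm, the detail of the explanation, the degree of encouragement and the timing of enrolment can all depend on it, deliberately or not. Two products of the pilot are then exposed. One is the between-arm comparison, including the effect size that is to inform a definitive trial. The other is the information on recruitment, because agreement to take part would reflect arm-dependent persuasion. The Recruitment plan allows for refusal by more than half of those approached, so persuasion has room to matter.

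A related question is whether the person who knows the allocation is kept apart from the person who assesses outcomes. The article claims rater blinding but does not describe that separation.

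**Working it through.** This is a question of trial conduct, so the main check sets the statements side by side.

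**1. Who could know what, and when**

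| Step | Who acts | Contact with the sequence, as written |
|---|---|---|
| First information and consent to be contacted | Clinician | None stated |
| Detailed explanation | A researcher | See next steps |
| Written consent | Not named (passive voice) | Not stated |
| Allocation | The researcher | Consults the sequence |
| Supply of the sequence | Offsite statistician | Generates and provides it |
| Assessment at 3 and 6 months | Not named | Not stated |

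**2. Concealment.** The allocation sentence speaks of *the* researcher, two sentences after *a* researcher was introduced as the person who explains the study. The natural reading is that they are the same person. What that person consults is a sequence, not a single assignment. The statistician's stated task is to provide it; nobody is said to hold it back or to release assignments one by one. No envelope, telephone or web step is mentioned. A procedure followed as written would let the recruiter see upcoming assignments.

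**3. Where influence could enter.** The clinician informs consecutive patients and is not given the sequence, so first identification is outside the problem. What remains is everything between the clinician's referral and enrolment.

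**4. Rater blinding.** Methods and the abstract state it. No section names the assessor, says that the allocating researcher also assesses, or says that a different person does. The statement is therefore neither supported nor contradicted by the described procedure.

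**5. Size.** The document gives no standard deviation, no effect size and nothing on how a recruiter might behave. Two illustrations, both on assumptions that are not in the document, show how far the answer depends on them:

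- *Deterrence.* Assume half of eligible women have a poor prognosis, with a 1 SD gap between the prognosis groups, and that a fraction f of the poor-prognosis women is deterred when the next place is C-MAPS. The poor-prognosis share in that arm becomes p = 0.5(1 − f) / [0.5(1 − f) + 0.5], and the arms differ by (0.5 − p) × 1 SD.
  - f = 0.10: p = 0.45/0.95 = 0.474, difference 0.03 SD
  - f = 0.25: p = 0.375/0.875 = 0.429, difference 0.07 SD
  - f = 0.50: p = 0.25/0.75 = 0.333, difference 0.17 SD
- *Substitution.* Assume equal arms of 30/2 = 15, and that k of the 15 C-MAPS places go to women scoring 1 SD lower than an unsteered recruit. The shift is k/15 SD: 3/15 = 0.2 SD for k = 3 and 6/15 = 0.4 SD for k = 6.

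The range of 0.03 to 0.4 SD comes entirely from the assumptions. These are raw shifts, before the adjustment for baseline differences planned in the Quantitative Analysis section. That adjustment would remove part of a shift that runs through measured variables, but not one that runs through unmeasured prognosis.

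**6. Sample size.** The planned 30 does not bear on the point. With equal groups of 15 it leaves 10 per group at a loss of up to 1 − 10/15 = one third. A concealed procedure leaves it unchanged.

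**The case against.** The strongest reply is that this is a condensed article. A sequence provided by the offsite statistician could in practice be released case by case or in sealed form, the researcher who allocates could be another team member, and the full protocol may say so. Part of this stands: it cannot be asserted that the allocation *is not* concealed, that the list is kept on site, or that the recruiter knows every upcoming assignment. But the article does not simply leave the step out. It states a mechanism, and that mechanism as written is open to the recruiter.

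A second reply is that clinicians first inform consecutive patients. This also stands: the document does not support the claim that the choice of whom to approach in the first place could depend on the next arm. It does not cover explanation, encouragement and timing after referral.

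A reader might go further and infer that the researcher who reads the list also rates outcomes, so that the trial contradicts its own claim of rater blinding. The document does not support this. Concealment before assignment and blinding at assessment are different safeguards, and failure of one does not break the other. The assessor is not identified, and the article mentions other staff: the offsite statistician, the recruiting clinicians, a senior psychiatrist who trains the therapists, and further research team members who take part in the qualitative analysis. In addition, the primary outcome and the Beck hopelessness and depression scales are self-report and the 6-month follow-up is by post or telephone, which limits what a rater could influence.

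Finally, this is a 30-participant pilot, not a definitive trial. That lowers the stakes of its comparison, but its estimates are intended to shape the definitive trial.

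**Conclusion.** The point holds in this form: as the Recruitment plan describes it, allocation concealment is not protected, because the researcher who explains the trial before consent also consults the sequence and no barrier to upcoming assignments is stated. This rests on reading the researcher in the two sentences as the same person, which is the natural reading but not the only possible one.

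The consequence is possible bias in the between-arm comparison and in the recruitment estimates, through the researcher's conduct after the clinician's referral. Its size cannot be derived from the document, and neither illustration above should be taken as an estimate.

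The rater-blind statement is unsupported by the described procedure but not contradicted by it. That is a gap to close in the same edit, not a demonstrated failure of blinding.

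The correction belongs before enrolment, because selection that has already occurred cannot be fully repaired in the analysis.

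**What to change.** Replace the allocation sentence in the Recruitment plan with:

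> The offsite statistician keeps the sequence and releases one allocation at a time, only after written consent and the completed baseline assessment are logged for that participant. The allocation goes to a team member who does not assess outcomes; this person informs the participant (C-MAPS or TAU) and, for C-MAPS, the therapist. Whoever does the 3- and 6-month assessments has no access to the sequence or the allocations.

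Naming who tells the participant matters because women in the treatment-as-usual group have no trial therapist through whom the news would reach them.

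The cost is one message and possibly a short wait per participant, 30 in total. It also requires someone in the team who does not assess outcomes to receive the allocations; the article gives no staffing figures, so the sponsor should confirm that such a person is available. The sample size and the planned analysis are unaffected. If the trial already works this way, only the wording needs correcting.

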### Description of intervention

This is a manualised intervention which was adapted from a self-help guide called "Life after self-harm" (Schmidt and Davidson 2004) based on the principles of cognitive behavioural therapy. This intervention includes evaluation of the self harm attempt, crisis skills, problem solving and basic cognitive techniques to manage emotions, negative thinking and relapse prevention strategies. This was chosen as there is consistent evidence in literature showing that people who self-harm have poor problem solving skills which may lead to hopelessness and depression.

A multidisciplinary focus group of mental health professionals initially translated the content of the manual into Urdu giving special consideration to cultural adaptation of phrases and concepts to reflect South Asian culture. Culturally appropriate case scenarios were incorporated and a consensual view to address cultural factors such as gender roles, sexuality, and substance misuse and family conflicts were taken. Due to low prevalence of substance misuse in South Asian women, issues related to this were replaced with emphasis on family conflicts.

The intervention will be delivered by qualified mental health professionals who underwent intense group training delivered by a senior psychiatrist. Ongoing training and supervision will be continuing throughout the course of the study.

C-MAPS (Culturally Adapted Manualized Problem Solving Training) will be a brief problem focused therapy comprising of 8 sessions delivered within 3 months after a self-harm episode. We will have two engagement sessions before the actual therapy. The session will involve in-depth explanation of the intervention, will address any concern or anxieties patients may have and will help in building better rapport between the patient and therapist. The adapted therapy will be delivered by therapists in the patient's home/GP practice/hospital depending upon patient's choice. Sessions will be offered weekly in the first month and than fortnightly and will last up to 50 minutes. The treatment will be structured around patient's current problems and helping the patient to deal with specific problems leading to the self harm act. The patients will be able to use this structure and approach in future recurrence.

#### Adaptation of the manual

There is sufficient evidence to suggest that cognitive behaviour therapy might need adaptation for use with ethnic minority clients in the west [21]. It has been suggested that therapists need to be aware of the cultural issues for successfully applying therapy. Assessment needs to take into consideration factors which are relevant to culture and religion of the client. Engagement has been described to be a major barrier in providing therapy in this client group. Finally, therapy techniques might need minor adjustments [22]. Involvement of family can be helpful and therefore family education and involvement where clients are comfortable with this will be tried in all cases. As mentioned above family conflicts are common in this group and therefore an additional session will focus on use of culturally sensitive training in assertiveness and conflict management. The process of adaptation will consist of two steps. In the first step therapists will be trained in culturally sensitive therapy through a workshop. They will also receive supervision throughout the project. The second phase of adaptation will consist of further refinement of manual based on information from our qualitative study.

